### Aims and hypotheses

The aim of the current study is to test the effectiveness of 30 hours of computer-based SocialVille training to improve social cognition and functional outcome in schizophrenia, compared with an active control intervention. Based on our previous findings, we predict that the SocialVille group will show statistically greater gains on co-primary outcome measures of social cognitive performance and functional performance as well as secondary measures of social cognition, functional capacity, functional outcome, motivation, and quality of life, indicating that SocialVille drives generalized social cognitive improvements as well as real-world functional improvements. Secondary aims include determining which patients best respond to SocialVille, and evaluating the effects of SocialVille training on low-level vs. high-level social cognition factors. For treatment response, we will examine predictors of social cognitive gains based on baseline participant demographic, symptom severity level, prior computer use, and functional measures, as well as on learning rate and plateau performance measures derived over the course of SocialVille use. Based on our previous studies, we hypothesize that most baseline measures will not define responder/non-responder groups effectively (except potentially for symptom severity), while baseline exercise performance, learning rate and plateau performance during SocialVille use will predict overall gains. Finally, we will separately examine the effects of training on the independent social cognitive factors of low-level social cue detection and high-level inferential process. We hypothesize that both low-level and high-level social cognition factors will be significantly correlated with functional capacity and real-world social and role functioning.

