In addition, to identify variables that predict treatment success in the SocialVille group, we will use an individual differences approach [80] and test for associations between not only outcome variables and pre-test scores (raw and composite), but also between outcome variables and improvements in aspects of the training tasks. This will help us determine if specific types of patients benefit from training more than others as well as if particular improvement patterns on training (i.e., training strategies) are predictive of successful outcomes. These analyses will be evaluated after correcting for multiple comparisons (i.e., Bonferroni).

Finally, following the main analyses, we will construct two separate composites, of low-level and high-level SC assessments, respectively, and test the effects of training on each of these composites using a linear mixed-effects model. We will further examine correlations between magnitude of change on each of the constructs and % improvement on SocialVille exercises.

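### Baseline predictors of response are sought in the SocialVille arm alone, which cannot show which patients benefit more from training

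*Protocol article*

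**What the plan says.** Under Data Analysis, the protocol article states: "to identify variables that predict treatment success in the SocialVille group, we will use an individual differences approach". The method is to "test for associations between not only outcome variables and pre-test scores (raw and composite"), and also to relate outcome variables to improvement on the training tasks. The inference follows directly: "This will help us determine if specific types of patients benefit from training more than others". The safeguard named is a multiplicity correction: "These analyses will be evaluated after correcting for multiple comparisons (i.e., Bonferroni").

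Aims and hypotheses describes the same secondary aim in terms of gains: "we will examine predictors of social cognitive gains based on baseline participant demographic, symptom severity level, prior computer use, and functional measures", together with learning rate and plateau performance during SocialVille use. It also records a prior expectation: "we hypothesize that most baseline measures will not define responder/non-responder groups effectively (except potentially for symptom severity").

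Neither section brings the control arm into this analysis. Yet the section on the repeated assessment battery gives the same assessments to both arms.

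**The concern.** In this trial, benefit means improvement on SocialVille compared with the active control. Whether benefit differs between types of patient is therefore a question about predictor-by-group interaction. Within the treated arm, a variable that modifies the effect of training cannot be told apart from one that predicts change under either programme. The article itself recognises such non-specific change: it uses alternate test forms to limit retest effects, and it justifies the control programme as a control for placebo and other non-specific effects. The predictor analysis leaves that control out.

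A second problem arises on one reading. If the outcome is a gain (post minus pre) and the predictor is the pre-test score of the same measure, or a composite containing it, the two share measurement error. They are then negatively correlated even when every patient benefits equally. Bonferroni limits the number of chance findings; it does not remove a bias.

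At stake is a statement about who should be offered SocialVille that has no comparative evidence behind it.

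**Working it through.** **The plan's own figure.** The predictor analysis has no stated figure. The trial size is 64 completers per arm for d = 0.50. With two-sided alpha 0.05 (my assumption, as the sample size section gives neither alpha nor power), the noncentral t distribution gives 80.1% power at 64 per arm. I use n = 64 for the SocialVille arm.

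**Inputs for test-retest correlation r.**
- MSCEIT 0.86 and Empathic Accuracy 0.72 (Social Cognitive Outcome Measure).
- UPSA-2 0.63 to 0.80 (Functional Capacity Outcome Measure).
- An implied value from the sample size section. It gives 10 points as two thirds of a standard deviation, so the index SD is 15. Reading its variance of 10 points as the SD of change, 10² = 2 × 15² × (1 − r), so r = 1 − 100/450 = 0.778.

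**Spurious correlation.** Assume the same benefit for everyone and equal pre and post variances σ². Then Cov(pre, gain) = −(1 − r)σ² and Var(gain) = 2(1 − r)σ², so

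corr(pre, gain) = −√((1 − r)/2).

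**Chance of a significant result.** By Fisher's z, the standardised mean is m = atanh(|corr|) × √(64 − 3). The chance is Φ(m − z), with a negligible second tail. The number of tests is not stated. I assume 10 (threshold 0.05/10 = 0.005, z = 2.807) and also show 20.

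Example, r = 0.778: corr = −√(0.222/2) = −0.333; m = 0.3466 × 7.810 = 2.707; Φ(2.707 − 2.807) = Φ(−0.100) = 46%.

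| r | Source | corr | 10 tests | 20 tests |
|---|---|---|---|---|
| 0.63 | UPSA-2, lower | −0.43 | 78% | 72% |
| 0.72 | Empathic Accuracy | −0.37 | 60% | 52% |
| 0.778 | implied by sample size section | −0.33 | 46% | 38% |
| 0.80 | UPSA-2, upper | −0.32 | 40% | 32% |
| 0.86 | MSCEIT | −0.26 | 25% | 18% |

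At r = 0.778 the chance falls further, to 28% with 50 tests and 22% with 100.

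**Simulation** (4,000 trials, 64 per arm, no true effect modification, r = 0.778):
- Pre-test against gain in the SocialVille arm: significant in 77% of trials at 0.05 and in about 46% at 0.005.
- The same test in the control arm: 78% at 0.05. The association says nothing specific to SocialVille.
- Group-by-baseline interaction using both arms: 4.9% at 0.05 and 0.7% at 0.005, close to nominal.
- Pre-test against post-test score in the SocialVille arm: significant at 0.05 in essentially every trial. This is prognosis.
- A separately measured baseline variable against gain, with a correlation of 0 to 0.4 with the true level: 5.0% to 5.4% at 0.05. There is no regression-to-the-mean bias here.

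**The case against.** The strongest objection is that no sentence in the article pairs a gain with its own pre-test score. Aims and hypotheses speaks of gains but lists demographics, symptom severity, computer use, functional measures and SocialVille learning measures as predictors. Data Analysis names pre-test scores but pairs them with outcome variables. The pairing is plausible but inferred, and this stands: the regression-to-the-mean part is conditional.

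A reader might infer that the trial will find a false baseline predictor, or will conclude that patients with worse baseline scores respond best. The documents do not support either. With the planned Bonferroni correction and 10 tests, the chance per measure is below one half at the implied r and about 25% for MSCEIT. Across several measures at least one false finding would be more likely, but that calculation needs the measures to be independent and the number of tests to be known. The authors also expect most baseline measures not to predict response.

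The choice of r matters as well. The UPSA-2 range covers follow-up of up to 36 months, against 10 to 12 weeks of training, and UPSA-2 is the functional measure, whereas the stated aim concerns social cognitive gains.

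Learning rate, plateau and training improvement on SocialVille exist only in that arm, so a single-arm analysis of them is unavoidable. Finally, the individual differences approach is defined by reference to the feasibility study, and testing for associations does not exclude adjustment for baseline. That could cure regression to the mean. It would not cure the single-arm restriction, which none of these objections answers.

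**Conclusion.** The point holds in a limited form. The article fixes the population (one arm), the test (association) and the inference (differential benefit), and the first two cannot support the third. This needs no numerical assumption and applies to every baseline predictor, including demographics and computer use, which regression to the mean does not bias.

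Regression to the mean is an added risk if outcome variables means gains and a gain is related to its own pre-test score or a composite containing it. Its size is then a correlation of about −0.26 to −0.43, significant in about 25% to 78% of trials per measure (about 46% at r = 0.778). These figures assume uniform benefit, equal pre and post variances, n = 64 and 10 tests at a family-wise 0.05; more tests lower them. If outcome variables means post-test scores, the association is prognostic.

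This is a secondary aim. The co-primary comparisons are not affected.

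**What to change.** For baseline predictors (demographics, symptom severity, computer use, functional measures, pre-test scores), test the predictor-by-group interaction on the post-training outcome (V6-V7), adjusted for the baseline score, in all randomised participants. Equivalently, add group × time × predictor to the planned mixed model. Keep Bonferroni and state the number of tests.

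Report the associations with SocialVille learning rate, plateau and training improvement as descriptive and within-arm, with the outcome adjusted for baseline, and claim no differential benefit from them. If the single-arm baseline analysis is kept, describe its results as prognostic associations only.

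The cost is a change of analysis wording, since the battery is already collected in both arms. The drawback is that interaction tests have less power than within-arm correlations, so a null result should be read with caution.

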### Overall Design and Timeline

The current study will employ a multi-site, longitudinal, blinded randomized controlled trial (RCT) design with a target sample of 128 patients with schizophrenia (see inclusion criteria below). This trial will follow the Consolidated Standards of Reporting Trials (CONSORT) guidelines [87] for the design, execution, and reporting of clinical trials, with the Non-Pharmacologic Treatment Interventions extensions to reflect the use of computerized social cognitive remediation as a treatment intervention.

Sixty-four patients with schizophrenia completing SocialVille will be compared to sixty-four patients with schizophrenia completing the active control condition (online computer-based games; see Fig. 1). Total participation time is approximately 12–14 weeks and includes seven (7) in-person assessment sessions. The first assessment session (V0) involves screening for eligibility (see inclusion/exclusion below). If the participant is eligible, they next perform two baseline assessment visit (V1-V2) to provide baseline level of their symptoms, social cognition, social functioning, functional capacity and motivation before training. After the baseline assessments, patients are randomized to either the SocialVille or control training program, and complete a set-up visit (V3) in which they are provided with a study laptop with their corresponding training program. Participants are then requested to complete 40 training sessions (about 10–12 weeks) of in-home training, while monitored remotely by a research assistant (cognitive remediation coach). Participants will be assessed again at the completion of 20 sessions (mid-intervention assessments; V4-V5) and at the completion of the entire training of 40 sessions (post-intervention assessments, V6-V7), to measure potential training-related improvements. After this visit (V7), participant activities are completed and trial participation ends. All assessments will be done by assessors that are blind to group affiliation.

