#### Social Cognitive Outcome Measure

The a priori co-primary social cognitive outcome measure will be a composite score comprised of a standardized, validated set of assessments that tap into low-level and high-level SC (social cognition) abilities (see [92]). A composite score will be derived from all five assessments to provide a social cognitive co-primary measure which encompasses several SC abilities. All assessments have been validated and used in outcome studies [68].

The low-level social cognitive assessments are:ER40 (The Penn Emotional Recognition Test)[93] is a computerized test to assess categorical identification of facial emotions. The tasks consists of 40 digital pictures of faces. The photos are presented individually and subjects are required to choose the most appropriate emotion label from five possible emotion choices (happiness, sadness, anger, fear, or no emotion). The 40 photos are of 8 actors, and there are 8 photos of neutral expressions, 4 low intensity and 4 high intensity photos for each emotion. The index of accuracy is the total number of correct items and response time. This measure was found to exhibit 70% accuracy of identifying emotions, with concurrent validity of .83, convergent validity of .79 and divergent validity of .09.PROID (Prosody Identification)[94] is a computerized vocal identification task used to assess a subject’s ability to perceive and discriminate emotion in the speech of others. All stimuli have been validated through trials with healthy controls.PFMT (Penn Faces Memory Test)[93] consists of 20 target faces and 40 foil faces; Stimuli are black and white photographs of faces, balanced for gender and age. All faces are of neutral expression. Participants are requested to view the pictures, and are then tested immediately and after a delay on the pictures they have seen, to determine if they were in the set they memorized or not.

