### Data Analysis

For the main analysis of this study (evaluating the efficacy of SocialVille as a treatment for social cognition deficits) we will define an Intent-To-Treat (ITT) population that includes all participants who have been randomized to either group. We will compare treatment and active control groups in the ITT population to determine if any differences in baseline demographic, characterization, outcomes variables, or total program use time remain after the randomization process.

We will test the following hypotheses of the primary outcomes, in addition to exploratory analyses: (1) Experimental treatment versus active control improves social cognition, and (2) Experimental treatment versus active control improves functional capacity. In addition, we will test the following hypotheses of the secondary outcomes: (1) Experimental treatment versus active control improves symptom severity; (2) Experimental treatment versus active control improves functioning; (3) Experimental treatment versus active control improves social cognition; (4) Experimental treatment versus active control improves motivation, and (5) Experimental treatment versus active control improves quality of life.

To examine each hypothesis, we will examine the data from each outcome measure(s) associated with the Primary or Secondary outcomes using a linear mixed-effects model with group and time as fixed factors, site as a random factor, and additional factors/covariates as required if there are trends towards significant baseline differences (p < 0.1) in the treatment and active control groups. Missing data will be handled with an iterative maximum likelihood procedure to optimally estimate model parameters. The key value for significance will be the group-by-time interaction term. This modeling will be conducted with a Type I error set at 0.025 for each model.

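### The predictor tests are fixed to Bonferroni, which is valid, but Holm's step-down procedure gives the same familywise control and never rejects less; the gain is small and free

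*Protocol article*

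**What the plan says.** The predictor analysis serves a stated secondary aim (Aims and hypotheses: "Secondary aims include determining which patients best respond to SocialVille"). Data Analysis sets it in one arm, "to identify variables that predict treatment success in the SocialVille group". It looks for associations of two kinds:

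- between "outcome variables and pre-test scores (raw and composite";
- "between outcome variables and improvements in aspects of the training tasks".

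It then fixes the correction: "These analyses will be evaluated after correcting for multiple comparisons (i.e., Bonferroni". The abbreviation used means *that is*, so the method is named and not offered as an example.

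Under Social Cognitive Outcome Measure the protocol article states: "A composite score will be derived from all five assessments". The social cognition composite and the raw scores that form it can therefore both be tested as predictors. The arm is planned at 64 completers (Overall Design and Timeline: "Sixty-four patients with schizophrenia completing SocialVille").

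The article gives no number of tests, familywise level, effect size or power for this analysis. The level it does state, "This modeling will be conducted with a Type I error set at 0.025 for each model", belongs to the outcome models.

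**The concern.** Bonferroni compares every p-value with the familywise level divided by the full number of tests. It does not relax after a rejection and makes no use of correlation between tests. Two better-known refinements do one or both:

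- **Holm** uses only the ordered p-values. After each rejection it divides by one test fewer. Its control holds under any dependence.
- **Westfall-Young step-down max-T** also steps down, and takes its critical values from the joint permutation distribution, so it benefits when scores overlap.

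At stake is some power to find true predictors in a single arm of 64. The article expects most baseline measures not to separate responders from non-responders. A missed predictor could be read as support for that expectation. No efficacy conclusion depends on this analysis.

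**Working it through.** **The plan's own figure.** None exists for the predictor tests. The only design figure is 128 completers for d = 0.50. With an assumed two-sided 0.05 and 80% power, n per arm = 2(1.960 + 0.842)²/0.50² = 62.8, so 63 per arm and 126 in total. The exact t test with 64 per arm has 80.1% power. This confirms 64 as the arm size and has no other bearing here.

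**Inputs.** From the article: n = 64. Assumed: familywise level 0.05 two-sided; true correlation r = 0.34 for each true predictor; m tests, of which k are true.

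**Step 1: dominance, without assumptions.** Order the p-values. Holm compares the j-th smallest with 0.05/(m − j + 1) and stops at the first failure. Each threshold is at least 0.05/m, so every Bonferroni rejection is also a Holm rejection. At j = 1 the two thresholds are equal, so Holm cannot help the first rejection.

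**Step 2: ceiling on the Holm gain.** With Fisher's z, the noncentrality is atanh(0.34) × √(64 − 3) = 0.354 × 7.810 = 2.766. Power at threshold a is about 1 − Φ(z(1 − a/2) − 2.766). Leaving aside false rejections, the easiest threshold a true predictor can meet is 0.05/(m − k + 1), after the other k − 1 have been rejected.

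| m | k | Bonferroni z | Power | Easiest Holm z | Power | Ceiling on gain |
|---|---|---|---|---|---|---|
| 12 | 6 | 2.865 | 46.0% | 2.690 | 53.0% | 7.0 points |
| 20 | 6 | 3.023 | 39.8% | 2.935 | 43.3% | 3.4 points |
| 20 | 2 | 3.023 | 39.8% | 3.008 | 40.4% | 0.6 points |
| 60 | 2 | 3.341 | 28.2% | 3.337 | 28.4% | 0.2 points |
| 100 | 5 | 3.481 | 23.7% | 3.470 | 24.1% | 0.3 points |

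**Step 3: gain actually reached.** The other true predictors are rarely all rejected first, so the average gain lies below the ceiling. Simulation at n = 64 and r = 0.34 gave these average powers per true predictor, Bonferroni / Holm:

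- m = 20, 1 true: 39.4 / 39.5%
- m = 20, 2 true: 40.7 / 40.9%
- m = 60, 2 true: 27.6 / 27.7%
- m = 100, 5 true: 23.5 / 23.6%
- m = 20, 6 true: gain about 1.5 points
- m = 12, 6 true: gain about 3 points

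**Step 4: what the overlap adds.** In a separate simulation, 20 pre-test scores included five tests correlated at an assumed 0.4 and their composite, with the rest correlated at 0.3. Average power per component was 39.1% with Bonferroni, 41.7% with Holm and 44.1% with step-down max-T. For the composite it was 85.5%, 85.5% and 87.0%. Over assumed correlations of 0.2 to 0.6, the 20 tests acted like about 13 to 18 independent ones.

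A further simulation, with five raw scores and their composite, put the familywise error of Bonferroni and Holm under no effect at the same 0.025 to 0.032 when the scores correlated at 0.8. Step-down permutation gave 0.045 to 0.061 (simulation error about ±0.014). The error allowance left unused through overlap is therefore recovered by the permutation test and not by Holm.

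**The case against.** The strongest reply is that Bonferroni is a valid, conventional choice for a secondary analysis, and that asking for Holm is taste. Validity stands in full. A reader might infer that counting a composite beside its own components makes the correction wrong; it does not, because Bonferroni holds under any dependence. A reader might also take the overlap as the reason to prefer Holm. It is not: Holm ignores correlation, and the overlap argues only for max-T.

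The second reply is that the gain nearly vanishes here. The article itself expects few baseline predictors. The family may also be large: SocialVille has 27 exercises, and testing each against two co-primary outcomes would already make 27 × 2 = 54 tests (an assumption, since the article gives no count). This too stands. Gains of 2 to 13 points for Holm do appear in simulations with only 6 or 12 tests, all of them truly associated. The article does not support that as a picture of this family.

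Third, permutation needs care: the trial is multi-site, the outcomes are plural and some data will be missing. That limits max-T and leaves Holm untouched. Holm also lacks Bonferroni's simple simultaneous confidence intervals, but the article promises none.

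What remains is that the article fixes a method which another equals or beats in every data set, at the same familywise error and without further assumptions.

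**Conclusion.** The point holds as a minor efficiency improvement to a secondary analysis. Bonferroni is valid but dominated by Holm. The direction is certain and needs no assumption about this trial, including how the tests are grouped into families. The size is illustrative: none for the first rejection, about 0 to 0.3 points of average power with 60 to 100 tests or few true predictors, and about 1.5 to 3 points with 12 to 20 tests of which 6 are true. These figures assume a familywise level of 0.05, r = 0.34 and complete data on 64 patients. The extra gain from max-T depends further on how strongly the scores correlate. It is not an error-rate fault and does not touch the co-primary tests.

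**What to change.** In Data Analysis, replace the parenthesis that names Bonferroni with Holm step-down, at the same familywise level, and do so before unblinding so that the change cannot look driven by the data. The cost is one phrase; no extra data, computing or assumption is needed.

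Optionally, specify Westfall-Young step-down max-T instead, to use the correlation between raw and composite scores. It should permute whole outcome rows jointly, within site, and state how missing data are handled. The cost is a short permutation run and that added specification.
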